| PATIENTS / GROUPS           | 
For the main “antiviral therapy” study currently 4 treatment arms are planned. Treatment arm 4 refers to standard of care (SOC) and will be the “control arm” of the study. A preliminary sample size calculation has been performed for the comparison of two groups based on a recent publication.
 
Therefore, we plan for n=100 patients per treatment arm in the main study. This number may increase after the interim analysis. This means that currently the main study is planned for approximately N=500 patients.
 
After inclusion of 20 and 50 patients per arm, interim analyses will be performed to draw conclusions on the sample size and to stop trial arms for safety or futility.
 
An even randomization ratio for “antiviral” arms (1:1:1:1) is theoretically intended but a dynamic assignment will occur according to available and permissible treatments (i.e. where no absolute contra-indication exists).
 |             |                             |             |                            |             |

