| 
COMPARATIVE
/CONTROL CONDITION
 | 
DRUG
 
Main Study:
Different “antiviral” treatment arms will be tested against each other and against SOC
 
Sub-study A:
Randomization will be carried out against standard of care which will likely include prophylactic doses of low molecular weight heparin.
 
Sub-study B:
randomized switch of patients with previously known and treated hypertension to non-RAS blocking agents (standard of care, e.g. nitrendipine, amlodipine or doxazosin) versus “stay-on-any-RAS-blockade”, or de novo treatment of patients with blood pressure >130/85mmHg in two consecutive measurements with RAS blocking agent (candesartan) versus non-RAS-blocking agents (e.g. nitrendipine, amlodipine or doxazosin), or no treatment, if blood pressure <140/90mmHg. RAS blockers will be compared vs. non-RAS blocking antihypertensive agents.
Healthy volunteers as another control group
 
Sub-study C:
Asunercept: Randomization will be done between groups receiving Asunercept at different dose levels (group 1: 25 mg; group 2: 100 mg; group 3: 400 mg) and best standard of care. Thus, there will be a 3:1 randomization between patients receiving verum and control patients. In case of a safety signal at interim analyses at a given dose, the arm will be terminated and patients will be switched to the remaining dose(s) which is/are tolerated. In case differences in efficacy are seen at interim analyses, patients will be switched from the less effective dose(s) to the more effective dose(s) or to equally effective lower dose(s)
 
Pentaglobin: Randomisation will be carried out against best standard of care (without IVIG or IL-6 blockage).
 |

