|  | 
There is currently only limited or no data available on expectable effect sizes. Therefore, we plan an interim analysis as soon as 20 and 50 patients have been randomized to the respective treatment arms. Study arms may be closed at interim analyses and after the second interim analysis, a sample size recalculation will be performed.
 
In short, n=100 per group for the asunercept (in total 400 patients) will be included. For the Pentaglobin part, n=20 will be included.
 
Statistical methodology
 
To test whether there is a difference between treatment arms, a log rank test will be performed at two-sided level alpha of 5%. The time-to-event data will be visualized by Kaplan-Meier plots.
 
Interim analysis
 
After inclusion of 20 and 50 patients per treatment arm.
 
The first interim analysis is mainly for safety and futility only. In the second interim analysis a sample size reassessment will be performed. To allow for early stopping in case overwhelming effects are observed, an alpha spending function with O'Brien and Fleming (OF) boundaries will be used.
 
For all sub-studies detailed statistical analysis plans will be created, which will also provide detailed information on sample size calculation.
 
Treatment arm four will only be analyzed in a descriptive manner.
 |

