## 8.2 Randomization and stratification

This is a randomized trial with different active treatments. However, for this platform trial, some special circumstances need to be considered. In the “Main” antiviral study three treatment options remain active within the randomized trial. Sub-study A, B, C, will also be conducted as randomized trials against standard of care. Randomization will be carried out online by [www.meduniwien.ac.at/randomizer](http://www.meduniwien.ac.at/randomizer). No stratification will be applied, except for the asunercept part of the trial. Based on the currently known risk factors, hospitalized patients are probably older and have more comorbidities, compared to a “general population”. Moreover, the sample sizes are relatively small, which precludes further stratification due to statistical reasons.

For sub-study B randomization will occur within the treatment group. In this cohort (labelled as “sub-study B”), patients with established arterial hypertension (and treatment) may be switched and patients with blood pressure  $\geq 130/85$  mmHg will be randomized to new treatments. Importantly, those patients with blood pressure  $\geq 130/85$  mmHg but  $< 140/90$  mmHg, who are randomized to non-RAS blocking treatment will not receive any treatment. Patients will be randomized to the following two treatment options using an allocation ratio of 1:1

- RAS blocker containing treatment (candesartan)
- Non-RAS blocker containing treatment (e.g. nitrendipin/amlodipin/doxazosin)

Thus, clinicians may decide within the first 24 hours if patients who participate in the main antiviral study A will also fulfill the criteria for one of the sub-studies. It is currently not intended to simultaneously enroll a patient in sub-studies A or B. Within sub-studies randomization will be done using the same software.

For sub-study C:

Asunercept: a 3:1 randomization against standard of care will be done, whereas three different doses of asunercept will be tested. Stratification according to the WHO scale at screening will be performed (only WHO scales 4, 5, and 6 are available for inclusion (patients with oxygen demand).

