## 11.6 Endpoints analysis

### 11.6.1 Primary endpoint analysis

All primary analyses will be on the modified ITT set and the analysis based on the per protocol set will be provided as supportive analysis.

The primary endpoint is time to clinical improvement which is defined as time from randomization to an (sustained) improvement of at least one category on two consecutive days compared to the status at randomization measured on a seven-category ordinal scale (proposed by WHO).

The 7-categories of the World Health Organization proposed scale, as follows:

1. Not hospitalized, no limitations on activities
2. Not hospitalized, limitation on activities;
3. Hospitalized, not requiring supplemental oxygen;
4. Hospitalized, requiring supplemental oxygen;
5. Hospitalized, on non-invasive ventilation or high flow oxygen devices;
6. Hospitalized, on invasive mechanical ventilation or ECMO;
7. Death.

During hospitalization this score will be determined daily (till day 29). If a patient is released from the hospital before day 29, the score will be determined at day 11 and 29 (and day 60 in clazakizumab arm) after randomization (depending when the patient was released or by telephone call).

The time to clinical improvement will be visualized by Kaplan-Meier Plots. The comparisons of the time-to-event curves will be performed using a log-rank at a two-sided level alpha of 5%.

(Please note in the initial phase only treatment arms (1-3, 5) might be available for the platform trial. A closed test procedure will be implemented to control the multiple level alpha. More details will be provided in the statistical analysis plan.

Additionally, a Cox-proportional hazard model will be performed. In this model we will use treatment as factor and it will be adjusted for calendar time to account for time trends (e.g. severity of cases might change over time).

Furthermore, we will include sex and age as factors in the model.

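### The protocol contradicts itself on whether standard of care, the control arm of the main study, is formally tested against or only described

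*Protocol*

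**What the plan says.** All references are to the protocol.

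- **Role of arm 4.** Synopsis, Patients/Groups: "Treatment arm 4 refers to standard of care (SOC) and will be the" control arm of the study. The investigational drug row also lists arm 4 as SOC.
- **Intended comparison.** Synopsis, comparative drug/control condition: the antiviral "treatment arms will be tested against each other and against SOC". Section 5.2 gives the same aim.
- **Analysis of arm 4.** Synopsis, end of the statistical methodology row: "Treatment arm four will only be analyzed in a descriptive manner". The sentence carries no condition, and the same row defines the log-rank test between treatment arms.
- **Arms named in the primary analysis.** Section 11.6.1 notes that "in the initial phase only treatment arms (1-3, 5) might be available for the platform trial". The next sentence reads: "A closed test procedure will be implemented to control the multiple level alpha". Details are left to the SAP.
- **Arms now open.** Section 8.2: "three treatment options remain active within the randomized trial". Section 7 (note to Figure 1) marks arm 1, hydroxychloroquine, as inactive, so the open arms are 2 (lopinavir/ritonavir), 3 (remdesivir) and 4 (SOC).
- **Size.** Synopsis, Patients/Groups: four arms, 100 patients in each, from which it concludes that "currently the main study is planned for approximately N=500 patients". Section 7.1.1 repeats about 500.

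**The concern.** Whether the control arm enters the primary test is a basic design decision, and the protocol fixes it in two opposite ways. An SAP author can refine the closed test, but on this question would have to follow one protocol statement and depart from the other.

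The stake is the main question of the antiviral study. A test of lopinavir/ritonavir against remdesivir has a null expectation if both work equally well and also if neither works. Without a test against SOC these two situations cannot be told apart, and the randomised SOC patients would support no inference.

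The arm list in section 11.6.1 and the stated total also disagree with the arms now randomised, so neither helps a reader decide which statement on SOC is current.

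**Working it through.** **1. The plan's own power figure.** Inputs from section 11.2: 100 per group, 154 events, hazard ratio 1.6 (medians 16 and 10 days; 16/10 = 1.6), two-sided alpha 0.05, stated power 83.15%.

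Log-rank approximation with equal allocation: power = Φ( (√E / 2) × ln HR − z₁₋α/₂ ).

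- √154 / 2 = 6.205; ln 1.6 = 0.470; product = 2.916.
- 2.916 − 1.960 = 0.956; Φ(0.956) = 83.05%.

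An exponential maximum-likelihood test with 100 per group and an assumed 28 days of follow-up expects 85.6 and 70.3 events. It gives 0.470 / √(1/85.6 + 1/70.3) − 1.960 = 0.960, so 83.15%. The per-pair calculation therefore reproduces, and 100 per arm is not in question.

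**2. What each reading leaves in the primary inference.** Three active arms give three pairwise contrasts.

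| Contrast | If arms are tested against SOC (comparative drug row) | If arm 4 is descriptive only (statistical methodology row) |
|---|---|---|
| Arm 2 vs arm 4 (SOC) | tested | not tested |
| Arm 3 vs arm 4 (SOC) | tested | not tested |
| Arm 2 vs arm 3 | tested | tested |

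The second reading keeps 1 of 3 contrasts and loses both control comparisons.

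**3. The arm list in section 11.6.1 against the arms defined.**

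| Arm | Defined in the protocol | Active | In the list (1-3, 5) |
|---|---|---|---|
| 1 hydroxychloroquine | yes | no | yes |
| 2 lopinavir/ritonavir | yes | yes | yes |
| 3 remdesivir | yes | yes | yes |
| 4 SOC | yes | yes | no |
| 5 | no | – | yes |

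The table of contents still gives arm 4 as IVIG under 9.1.1.3, while the body section with that number is arm 3, remdesivir. Section 7 still mentions immunoglobulin as a product awaiting availability. An older numbering, with arm 4 as IVIG and a fifth arm, would account for the list, the descriptive-only sentence and a total of 500. The protocol does not say so; this is an inference.

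**4. The total.** Total = arms × 100.

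- Four listed arms: 4 × 100 = 400. Stated 500 is 100 / 400 = 25% higher.
- Three active arms: 3 × 100 = 300. Stated 500 is 200 / 300 = 67% higher.
- Only 5 × 100 gives 500.

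**5. Power for the control comparisons once SOC is tested.** With 154 events per pair and hazard ratio 1.6, each comparison with SOC has 83.05% power at alpha 0.05. If alpha were split equally over two such comparisons (Bonferroni, 0.025 each; my assumption, since the protocol names only a closed test), then 2.916 − 2.241 = 0.675 and Φ(0.675) = 75.0%.

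**The case against.** The strongest reply is that the descriptive-only sentence stands alone. It appears only in the synopsis; section 11.6.1 contains no such restriction. The hypotheses and the log-rank test in the synopsis refer to treatment arms without excluding SOC. Section 5.2 and the comparative drug row state the comparison with SOC, and section 11 says each part of the study has its own control group randomised against standard of care. On this view the sentence is an uncorrected remnant about a different arm 4, not a decision to leave SOC out.

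Much of this stands, and it rules out three stronger readings that a reader might infer:

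- **That no antiviral can be tested against its control.** This follows only if the one sentence overrides every other statement. The documents show a contradiction, not a design without a control test.
- **That arms 1-3 and 5 are the closed-test family.** The text gives them as arms that might be available in the initial phase. The closed-test sentence names no arms or hypotheses, so the list does not show that SOC is excluded from the procedure.
- **That the total of 500 undermines the comparisons.** Power is planned per pair at 100 per arm and reproduces. The total is approximate, and arms may be added by amendment. Even so, 500 is presented as what 100 per arm currently means, and that arithmetic is wrong.

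The reply does not remove the conflict. The sentence is unconditional, uses the current number of the SOC arm and sits beside the definition of the primary test. The remnant explanation is plausible but unstated. Leaving closed-test details to the SAP is acceptable; leaving the protocol with two answers on the control comparison is not.

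**Conclusion.** The contradiction is real and must be resolved, because it decides whether the primary endpoint is tested against the control arm. Followed literally, the descriptive-only sentence would remove two of the three pairwise contrasts among active arms, including both against SOC. That size depends on giving the sentence precedence, which the documents neither require nor exclude.

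The list of arms 1-3 and 5 is out of date and fails to resolve the question, but is not itself evidence that SOC is outside the test. The stated total is a minor consistency error, 25% above the four-arm figure and 67% above the three-arm figure, with no effect on per-pair power. The older numbering is the likely origin, as an inference only.

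**What to change.** 1. In the synopsis statistical methodology row, delete or correct the descriptive-only sentence so that arm 4 (SOC) is an inferential comparator in the primary log-rank analysis, as the comparative drug row states. If the sentence was meant for another arm, name that arm.
2. In section 11.6.1, replace the list of arms 1-3 and 5 with the current arms, and state that the closed test includes arm 2 versus arm 4 and arm 3 versus arm 4. The remaining structure, including arm 2 versus arm 3, can be left to the SAP.
3. As a minor correction, restate the main-study total in the synopsis and section 7.1.1: 300 for the three active arms, plus any patients already randomised to inactive arm 1 (the protocol gives no count) and 100 for each arm added later. If all four listed arms are meant, the figure is 400.

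**Cost.** These are wording changes; at 100 per arm no extra patients or data are needed. The stated total falls. The protocol should also say that the 83% power applies per pair at alpha 0.05. Under the assumed Bonferroni split over two SOC comparisons it is about 75%, and a closed test may lose less.

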### 3 LIST OF ABBREVIATIONS

|        |                                                         |
|--------|---------------------------------------------------------|
| ADR    | Adverse Drug Reaction                                   |
| ACE-I  | Angiotensin Converting Enzyme inhibitor                 |
| ARB    | Angiotensin II Receptor Blocker                         |
| AE     | Adverse Event                                           |
| ALT    | Alanin Aminotransferase                                 |
| ARDS   | Acute Respiratory Distress Syndrome                     |
| ATP    | Adenosine Tri-Phosphate                                 |
| AST    | Aspartate Aminotransferase                              |
| BP     | Blood Pressure                                          |
| CRF    | Case Report Form                                        |
| CRO    | Clinical Research Organization                          |
| CSR    | Clinical Study Report                                   |
| DILI   | Drug induced liver injury                               |
| DOH    | Declaration of Helsinki                                 |
| DSUR   | Development Safety Update Report                        |
| ECG    | Electrocardiography                                     |
| EOS    | End of Study                                            |
| EU     | European Union                                          |
| GCP    | Good Clinical Practice                                  |
| GGT    | Gamma-Glutamyltransferase                               |
| HBsAg  | Hepatitis B Surface Antigen                             |
| HBV    | Hepatitis B Virus                                       |
| HCG    | Human Corionic Gonadotropin                             |
| HVC    | Hepatitis C Virus                                       |
| HIV    | Human Immunodeficiency Virus                            |
| ICH    | International Conference on Harmonization               |
| IEC    | Independent Ethics Committee                            |
| IMP    | Investigational Medicinal Product                       |
| ISF    | Investigator Site File                                  |
| ISO    | International Standardisation Organization              |
| KKS    | Koordinationszentrum für Klinische Studien              |
| LLT    | Lower level terms                                       |
| mm     | Millimeter                                              |
| mmol/l | Millimol/Liter                                          |
| RBC    | Red Blood Cells                                         |
| SAE    | Serious Adverse Event                                   |
| SAP    | Statistical analysis plan                               |
| SAR    | Serious Adverse Reaction                                |
| SOP    | Standard Operating Procedure                            |
| SUSAR  | Suspected Unexpected Serious Adverse Reaction           |
| TMF    | Trial Master File                                       |
| TRAIL  | Tumor necrosis factor related apoptosis inducing ligand |

|     |                           |
|-----|---------------------------|
| WBC | White Blood Cells         |
| WHO | World Health Organization |

| 14 REFERENCES                                                       | 83 |

Table 1 VISIT AND ASSESSMENT SCHEDULE

| PERIODS                          | Name     | SCREENING |               | TREATMENT          |                    |                                                                                             |                   |                    | FOLLOW-UP Treatment arms 1-4               | Follow-up substudies                       |
|----------------------------------|----------|-----------|---------------|--------------------|--------------------|---------------------------------------------------------------------------------------------|-------------------|--------------------|--------------------------------------------|--------------------------------------------|
|                                  | Duration |           |               | 28 days            |                    |                                                                                             |                   |                    | Day 29                                     | Up to 7 days after recovery                |
| VISITS                           | Number   | 1         | 2             | 3                  | 3 A                | 3 B                                                                                         | 3 C               | 4                  | 4                                          | 4                                          |
|                                  | Name     | Screening | Randomization | Treatment arms 1-4 | Substudy A         | Sub-study B                                                                                 | Sub-study C       | All treatment arms | Follow-up (Telephone call/inpatient visit) | Follow-up (Telephone call/inpatient visit) |
|                                  | Time     |           |               | Day 1-7, or longer | Days 1 - discharge | Days 1 - recovery                                                                           | Days 1 - recovery | Day 1-29           | Day 29 (±7)                                |                                            |
| Informed Consent                 |          | X         |               |                    |                    |                                                                                             |                   |                    |                                            |                                            |
| Inclusion / Exclusion Criteria   |          | X         |               |                    |                    |                                                                                             |                   |                    |                                            |                                            |
| Medical History                  |          | X         |               |                    |                    |                                                                                             |                   |                    |                                            |                                            |
| Concomitant/change in medication |          | X         | X             | X                  | X                  | X                                                                                           | X                 |                    | X                                          | X                                          |
| Physical Examination             |          | X         |               |                    |                    |                                                                                             |                   |                    | X, if possible                             | X, if possible                             |
| Body weight and height           |          | X         |               |                    |                    |                                                                                             |                   |                    | X, if possible                             | X, if possible                             |
| Vital Signs (BP, PR)             |          | X         |               | X                  | X                  | X (daily, self-reported, telephone or clinical visits 1x/week), or more often if necessary) | X                 |                    | X                                          |                                            |
| 12-lead ECG                      |          | X         |               |                    |                    |                                                                                             | X                 |                    | X, if possible                             | X, if possible                             |

|                                             |   |   |   |   |   |   |                          |                |                |
|---------------------------------------------|---|---|---|---|---|---|--------------------------|----------------|----------------|
| Laboratory Tests, incl. oropharyngeal swabs | X |   | X | X | X | X | 3x/week, until discharge | X              | X              |
| Pregnancy Test                              | X |   |   |   |   |   |                          | X, if possible | X, if possible |
| WHO-ordinal scale, NEWS                     | X | X |   |   |   |   | X                        |                |                |
| Study Drug Dispensing / Return              |   |   | X | X | X | X |                          | X              | X              |
| Adverse Events                              |   | X | X | X | X | X |                          | X              | x              |

